### Testing procedures for AMR

WHO EGASP guidelines and standard operating procedures will be adapted for use with pregnant women, and otherwise followed for AMR testing for NG.^38^ Nurse-collected cervical samples will be obtained using ESwabs (COPAN Diagnostics) from women initially found to be positive for NG using the Xpert assay. Speculum examinations will be conducted by nurses with many years of experience performing these examinations, using plastic disposable speculums. Samples will be plated onto the InTray GC (Biomed Diagnostics) in-vitro device, as will urethral samples collected from men. These will be subsequently incubated in the laboratory and minimum inhibitory concentrations of ceftriaxone, cefixime, azithromycin and ciprofloxacin will be determined using Etest (bioMérieux) and interpreted using the European Committee on Antimicrobial Susceptibility Testing standards.^39^

### Sample size calculations

There are limited data on STI prevalence in pregnant women in Zimbabwe. A prevalence of curable STIs between 32.0% and 37.0% has been reported in South Africa and Zambia.^12–16^ Our recent studies among female youth in Harare have demonstrated combined CT/NG prevalence between 18.2% and 19.5%.^18 19^ The prevalence of hepatitis B in pregnant women in South Africa has ranged between 3.1% and 5.3%.^20–22^ Therefore, a conservative estimate of composite prevalence of curable STIs and hepatitis B is 30.0%. With a desired precision of 3% and alpha of 0.05, a sample size of 896 is required. To allow for invalid test results, 1000 pregnant women will be screened. The minimum detectable ORs for factors associated with the presence of STIs at different composite prevalence of STIs are shown in table 3.

**Table 3 T3:** Minimum detectable ORs for factors associated with presence of STIs

Sample size*	STI prevalence	Precision	Smallest OR detected at 80% power	Smallest OR detected at 90% power
896	20%	2.6%	1.74	1.89
	25%	2.8%	1.67	1.80
	30%	3.0%	1.63	1.75

*Assuming a prevalence of a risk factor of 20% among those without STIs.

STIs, sexually transmitted infections.

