A group that may particularly benefit from the introduction of diagnostic testing for STIs is pregnant women. Pregnant women in LMICs are a high-risk population for STIs,^9^ and diagnosis and treatment may prevent adverse pregnancy outcomes and congenital transmission of some infections.^10^ As point-of-care (POC) testing for HIV and syphilis has already been integrated into antenatal care (ANC) services, this provides a platform for further STI testing and management and potentially enhances operational feasibility. In addition to curable STIs, this is also pertinent for hepatitis B, as testing is noted to be essential for the WHO’s triple elimination initiative, which aims to eliminate vertical transmission of HIV, syphilis and hepatitis B.^11^ Key to triple elimination is the provision of a multidisciplinary approach within routine ANC services.

There are limited data on STI prevalence among pregnant women in Zimbabwe. Prevalence of CT up to 26.0%, of NG up to 6.4% and TV up to 24.8% has been reported in pregnant women in South Africa and Zambia.^12–16^ A 2010 study found a TV prevalence of 11.8% and syphilis prevalence of 1.2% among pregnant women in Harare.^17^ Recent studies among female youth in Harare have demonstrated a combined CT/NG prevalence between 18.2% and 19.5%.^18 19^ A prevalence of hepatitis B ranging between 3.1% and 5.3% has been reported in pregnant women in South Africa.^20–22^

Control of STIs, particularly NG, is additionally compromised by AMR.^23^ Surveillance is key to identifying and monitoring AMR. WHO and the Centers for Disease Control, USA established the Enhanced Global Gonococcal Antimicrobial Surveillance Programme (EGASP) in 2015.^24^ A sample of at least 100 gonococcal isolates per year per country is recommended.^23^ However, gonococcal AMR data are still extremely limited and in 2018, only 5 of 47 countries in the WHO African Region reported susceptibility testing for NG of at least one of ceftriaxone, cefixime, ciprofloxacin and azithromycin.^25–28^

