### Statistical analysis

The primary outcome measure is the composite prevalence of CT, NG, TV, syphilis and hepatitis B in this population.

Other outcome measures include:

Individual prevalence of each STI (CT, NG, TV, syphilis, hepatitis B and HIV).Uptake of testing.Uptake of treatment.Uptake of partner notification.STI yield (number of participants with a positive STI result/total number of eligible individuals).Prevalence of AMR to ceftriaxone, cefixime, azithromycin and ciprofloxacin in NG isolates.Prevalence of preterm birth, miscarriage and low birth weight.

Categorical variables will be described using frequencies and percentages. Continuous variables will be described using either mean (SD) or median (IQR) for normally distributed and non-normally distributed data, respectively. Multivariable logistic regression will be used to assess factors associated with presence of STIs. Clustering will be adjusted for at clinic level. Logistic regression will also be used to assess the relationship between STI diagnosis and birth outcomes.

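### The 30% composite prevalence is not conservative for a ±3-point precision target: it lies below the cited 32–37% for curable STIs alone and leaves 896 evaluable women no slack (minor)

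*Protocol article*

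**What the plan says.** The primary outcome is a composite: "The primary outcome measure is the composite prevalence of CT, NG, TV, syphilis and hepatitis B in this population" (Statistical analysis).

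The Sample size calculations section builds up to its assumed value from three sources:

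- Regional curable STIs: "A prevalence of curable STIs between 32.0% and 37.0% has been reported in South Africa and Zambia".
- Local CT/NG: "Our recent studies among female youth in Harare have demonstrated combined CT/NG prevalence between 18.2% and 19.5"%.
- Hepatitis B: "The prevalence of hepatitis B in pregnant women in South Africa has ranged between 3.1% and 5.3"%.

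It concludes: "Therefore, a conservative estimate of composite prevalence of curable STIs and hepatitis B is 30.0"%. The next sentence fixes the size: "With a desired precision of 3% and alpha of 0.05, a sample size of 896 is required". The recruitment target follows: "To allow for invalid test results, 1000 pregnant women will be screened".

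Table 3, at a sample size of 896, gives precision of 2.6%, 2.8% and 3.0% at prevalences of 20%, 25% and 30%. Its smallest detectable odds ratios at 80% power are 1.74, 1.67 and 1.63. It has no row above 30%.

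The Introduction adds one more local source: "A 2010 study found a TV prevalence of 11.8% and syphilis prevalence of 1.2% among pregnant women in Harare".

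**The concern.** In a sample size calculation, a conservative assumption is one that makes the required number larger if it errs. For an absolute half-width, the required number is proportional to p(1−p), which rises until p = 0.5. Setting the prevalence low therefore makes the requirement smaller. Table 3 shows this: at a fixed 896, precision worsens as prevalence rises. A low prevalence is cautious only for the odds-ratio columns, and those do not determine 896.

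The value chosen is also below part of its own evidence. A composite that includes the curable STIs and adds hepatitis B cannot be lower than its curable part. Yet 30.0% is under the whole cited regional range for curable STIs alone. This needs no assumption about co-infection. It assumes only that the infections counted in the cited figure are among those in the composite.

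What is at stake is the stated precision of the primary outcome, which the article describes as high in both its strengths list and its Discussion. No hypothesis test or decision rule depends on it.

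**Working it through.** **Formulae.** Required number: n = 1.96² × p(1−p) / d², with d = 0.03. Half-width at N evaluable women: 1.96 × √[p(1−p)/N].

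**Step 1: reproduce the plan's figures.** At p = 0.30: 3.8416 × 0.21 / 0.0009 = 896.4, against 896 stated (897 if rounded up, which is immaterial). Half-widths at N = 896 for 20%, 25% and 30% are 2.62, 2.84 and 3.00 points, against 2.6, 2.8 and 3.0 in Table 3. The arithmetic is right, and at 30% the target is met with nothing to spare.

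**Step 2: prevalences that follow from the cited figures.**

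- Regional, curable STIs alone: 32.0–37.0% (as stated).
- Regional with hepatitis B, assuming independence: 1 − 0.68 × 0.969 = 34.1%; 1 − 0.63 × 0.947 = 40.3%.
- Regional with hepatitis B, assuming no overlap: 32.0 + 3.1 = 35.1%; 37.0 + 5.3 = 42.3%.
- Harare CT/NG, TV and syphilis with the South African hepatitis B range, assuming independence: 1 − 0.818 × 0.882 × 0.988 × 0.969 = 30.9%; 1 − 0.805 × 0.882 × 0.988 × 0.947 = 33.6%.
- The same Harare low-end inputs with co-infection, assuming for illustration that half of TV cases also have CT/NG: CT/NG or TV = 18.2 + 5.9 = 24.1%; then 1 − 0.759 × 0.988 × 0.969 = 27.3%.

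Only the first line is stated in the protocol. The others depend on the overlap assumption named.

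**Step 3: precision and required number at those values.**

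| Prevalence | n for ±3 points | Half-width, N = 896 | Half-width, N = 1000 |
|---|---|---|---|
| 30.0% | 897 | 3.00 | 2.84 |
| 30.9% | 912 | 3.03 | 2.86 |
| 32.0% | 929 | 3.05 | 2.89 |
| 34.1% | 960 | 3.10 | 2.94 |
| 37.0% | 995 | 3.16 | 2.99 |
| 40.3% | 1027 | 3.21 | 3.04 |
| 42.3% | 1042 | 3.23 | 3.06 |

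**Step 4: how far the 1000 helps.** The rise from 896 to 1000 allows 1 − 896/1000 = 10.4% non-evaluable results at 30%. The room shrinks with prevalence: at 32%, 1 − 929/1000 = 7.1%; at 37%, 1 − 995/1000 = 0.5%. With all 1000 evaluable, ±3 points holds while p(1−p) ≤ 0.0009 × 1000 / 3.8416 = 0.2343, that is, up to p of about 37.5%.

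No design effect for clinics is included in any of these figures.

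**The case against.** The strongest reply is that nothing is miscalculated and little is lost. The 896 and the precision column of Table 3 both reproduce. The protocol says that data on pregnant women in Zimbabwe are limited. The regional figures come from other countries, the CT/NG figures from female youth, and the TV and syphilis figures from a 2010 study. Choosing 30% among such sources is a judgement. STIs share risk factors, so co-infection is plausible and could bring the Harare composite below 30%, where 896 is more than enough. The study also screens 1000 women, and the protocol nowhere predicts that a tenth of results will be invalid.

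Most of this stands, and it limits the point. A reader might infer that the plan expects 31–42% and so is bound to miss its target. The documents do not support that. The only composite they state is 30.0%, and the wider range comes from independence or no-overlap assumptions. A reader might also infer that Table 3 was cut off to show only favourable rows. That is not supported either: the table is introduced for minimum detectable odds ratios, for which 20–30% is the less favourable side.

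What the reply does not rescue is the label. The value is called conservative and then used to fix the number for a precision target, where a low value works the other way. The regional range for curable STIs is above 30% whatever the overlap. The 1000 is justified only as cover for invalid results; to the extent that it is used for that, it cannot also absorb a higher prevalence.

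**Conclusion.** Wrong as written, but minor. The value of 30.0% is conservative for the detectable odds ratios and not for the precision calculation that sets 896. With 896 evaluable women, the half-width is 3.05–3.16 points at the cited 32–37%, and about 3.1–3.2 points at 34–40% once hepatitis B is added under independence. The largest excess over the target, at the no-overlap extreme of 42.3%, is 0.23 points.

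The shortfall is firm if prevalence is in the cited regional range and only about 896 results are evaluable. It is conditional on limited co-infection for the Harare figures, which give about 31–34% under independence. It disappears up to about 37.5% if nearly all of the 1000 are evaluable. It does not threaten the usefulness of the primary estimate.

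**What to change.** 1. Remove the description of 30.0% as conservative from the precision calculation, or say that it applies only to the minimum detectable odds ratios.
2. Add rows for 35% and 40% to Table 3. Precision at 896 is ±3.1 points (1.96 × √(0.35 × 0.65/896) = 3.12) and ±3.2 points (1.96 × √(0.40 × 0.60/896) = 3.21). At 1000 both are about ±3.0 points (2.96 and 3.04). The odds-ratio cells should be filled by the method used for the existing rows.
3. State the expected precision as about ±3.0–3.2 points, depending on prevalence and the number evaluable, before any allowance for clustering by clinic.

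The cost is one sentence and two table rows. The stated precision becomes slightly less favourable. No extra enrolment or change to the analysis is needed.

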## Methods and analysis

### Study design and setting

A prospective interventional study will be conducted in primary healthcare clinics (PHCs) in Harare province, Zimbabwe. The PHCs are all based in urban, high-density settings, and provide nurse-led services including ANC and uncomplicated deliveries. High-risk women receive their ANC at central hospitals, with referral also available if complications develop in labour. Opt-out HIV and syphilis testing using rapid diagnostic tests is part of routine care. GeneXpert devices are often available for tuberculosis diagnosis, but the study will provide an additional machine to ensure that sufficient diagnostic capacity is available. We previously demonstrated the feasibility of using non-laboratory technicians to operate the GeneXpert device for on-site CT/NG testing in community settings in Bulawayo, Zimbabwe.^29^

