## Discussion

There is mounting evidence that syndromic management is not an effective method for the control of STIs.^14 40 41^ However, evidence is required by national and international policymakers to inform how to transition towards diagnostic testing for STIs. We anticipate high prevalence of STIs among pregnant women in this study, thus providing additional evidence that new strategies are required for control of STIs in Zimbabwe. The data on acceptability, feasibility and cost-effectiveness will provide guidance on how best to implement new strategies for a package of integrated diagnostic testing in ANC. Furthermore, this study will provide baseline data for the design of future testing strategies, implemented at a larger scale and potentially as part of a cluster-randomised trial to demonstrate efficacy.

The IPSAZ Study has several strengths. The large sample size ensures that STI prevalence in the antenatal population in Harare will be estimated with high precision. The use of mixed methods for the process evaluation will enable quantitative and qualitative data to complement and inform each other. Furthermore, the economic evaluation will inform policymakers about whether introducing such a testing programme represents a cost-effective use of health resources in this and similar contexts. Finally, we will be following adapted EGASP standard procedures for gonococcal culture and AMR testing. EGASP guidelines do not currently include provision for sample collection from pregnant women and are focused on symptomatic men. Our experience will therefore inform the potential expansion of EGASP guidelines to include pregnant women, and to consider the use of antenatal networks as a platform for gonococcal surveillance for future national EGASP programmes.

We acknowledge some limitations. There is no formal outcome evaluation comparing birth outcomes between those who received the intervention and those who did not. This is an important research question. Although treatment of STIs is likely to prevent complications such as pelvic inflammatory disease, there is conflicting evidence on whether provision of treatment for STIs during pregnancy prevents adverse birth outcomes.^42–44^ Future studies need to investigate the clinical effectiveness of scaling up of STI testing and treatment in ANC.

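### The 896 women and the ±3% precision assume independent women, although the article acknowledges clustering by clinic and claims precision for all of Harare's antenatal population

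*Protocol article*

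**What the plan says.** The primary outcome is one proportion: "The primary outcome measure is the composite prevalence of CT, NG, TV, syphilis and hepatitis B in this population" (Statistical analysis). The Sample size calculations section sets its anticipated value: "Therefore, a conservative estimate of composite prevalence of curable STIs and hepatitis B is 30.0" per cent. It then gives the size: "With a desired precision of 3% and alpha of 0.05, a sample size of 896 is required". The recruitment target is higher, for one stated reason: "To allow for invalid test results, 1000 pregnant women will be screened". Table 3 lists the precision at 896 women as 2.6%, 2.8% and 3.0% for prevalences of 20%, 25% and 30%, next to minimum detectable odds ratios.

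On clinics, Study design and setting says: "A prospective interventional study will be conducted in primary healthcare clinics (PHCs) in Harare province, Zimbabwe". The number of clinics is not given. Statistical analysis says, directly after the sentence on the risk-factor regression: "Clustering will be adjusted for at clinic level".

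On the target population, the Discussion says: "The large sample size ensures that STI prevalence in the antenatal population in Harare will be estimated with high precision". The strengths and limitations box makes a similar claim for antenatal attendees in Harare.

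**The concern.** The sample size section and the rest of the article rest on different assumptions. The first treats each woman as an independent draw. The analysis section recognises that women from the same clinic may resemble one another, and the Discussion generalises beyond the clinics sampled. For that wider population, variation in prevalence between clinics is part of the sampling error, and a formula that omits it understates the interval width.

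What is at stake is the stated precision of the primary outcome, which the article lists among its strengths. An interval that ignores clinics would be too narrow for a Harare-wide statement. An interval that allows for them would probably be wider than the ±3% readers have been led to expect.

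**Working it through.** **Inputs from the article:** prevalence p = 0.30, half-width d = 0.03, alpha 0.05 (z = 1.96), 896 women required, 1000 screened.

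**Step 1: reproduce 896.** n = z² p(1 − p) / d² = 1.96² × 0.30 × 0.70 / 0.03² = 896.4. The stated figure reproduces with no design effect.

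**Step 2: reproduce Table 3.** Half-width = 1.96 × √(p(1 − p)/896):
- 20%: 2.62%
- 25%: 2.84%
- 30%: 3.00%

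All three match the printed column. The odds ratios also reproduce without a clustering term: a continuity-corrected comparison of two proportions, with the risk factor at 20% among women without STIs, needs 889 to 901 women in total.

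**Step 3: add a design effect.** For k clinics of equal size, DEFF = 1 + (N/k − 1) × ICC, and half-width = 1.96 × √(0.21 × DEFF / N). The article gives neither k nor the ICC, so the values below are assumptions: k = 4, 6, 10 and ICC = 0.001 to 0.02.

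Half-width (± percentage points) at 30% prevalence:

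| Clinics | Women | ICC 0.001 | ICC 0.005 | ICC 0.01 | ICC 0.02 |
|---|---|---|---|---|---|
| 4 | 896 | 3.3 | 4.4 | 5.4 | 7.0 |
| 6 | 896 | 3.2 | 4.0 | 4.7 | 6.0 |
| 10 | 896 | 3.1 | 3.6 | 4.1 | 5.0 |
| 4 | 1000 | 3.2 | 4.3 | 5.3 | 7.0 |
| 6 | 1000 | 3.1 | 3.8 | 4.6 | 5.9 |
| 10 | 1000 | 3.0 | 3.5 | 4.0 | 4.9 |

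One cell in full: for 6 clinics and ICC 0.01 at 896 women, DEFF = 1 + (149.3 − 1) × 0.01 = 2.48. The half-width is 3.00 × √2.48 = 4.7%, and the effective sample is 896/2.48, about 361.

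Only one cell stays within ±3%: 10 clinics, ICC 0.001 and all 1000 women analysable (2.98%).

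**Step 4: find how much clustering ±3% can absorb.** At 896 women there is no headroom, so any positive ICC exceeds ±3%. If all 1000 women gave usable results, the largest tolerable design effect is 1000/896.4 = 1.116. The largest ICC is then 0.116 / (1000/k − 1):
- 4 clinics: 0.116/249 = about 0.0005
- 6 clinics: 0.116/165.7 = about 0.0007
- 10 clinics: 0.116/99 = about 0.0012

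The between-clinic standard deviation is √(ICC × 0.21). These limits correspond to about 1.0, 1.2 and 1.6 percentage points, so clinics would have to be nearly identical in prevalence. An ICC of 0.01 corresponds to about 4.6 points.

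**The case against.** The strongest reply is that the calculation contains no error. The 896, the three precisions and the odds ratios all reproduce, and the independence formula is acceptable if inference is confined to the participating clinics, treated as fixed strata. The article describes consecutive enrolment and no random sampling of clinics, and it defines the outcome for its study population. This stands as a legitimate framework. However, the article does not say that it adopts it, and the Discussion and the strengths box claim the wider population.

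Second, the clustering sentence follows the risk-factor regression. A reader might infer that the plan commits to a clinic-adjusted interval for the primary prevalence, and that the sample size contradicts the primary analysis outright. The text does not support that, because use of the adjustment for the primary estimate is implied at most. The mismatch with the Harare-wide claim remains either way.

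Third, a reader might conclude that the design fails to deliver ±3%. That is not established. The loss depends on two quantities the article does not give, and it could be negligible if clinics hardly differ. The wide end of the table is not a forecast.

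Fourth, precision is not the only justification of size, since Table 3 also gives detectable odds ratios.

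Finally, a condensed article may leave the number of clinics and the ICC to the full protocol. Their absence is not the point here. The point is that a printed precision and a printed strength rest on an assumption the article does not make elsewhere.

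**Conclusion.** The point holds in a limited form. The 896 and the 2.6%, 2.8% and 3.0% in Table 3 are correct only with a design effect of 1, while the article acknowledges clinic-level clustering and claims precision for Harare's antenatal population. The extra 104 women (1000 − 896) are set aside for invalid tests and are not a clustering allowance.

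For that population, any appreciable ICC takes the primary prevalence beyond ±3%. The size rests on assumed values, equal clinic sizes and a normal-approximation interval. A t-based interval with few clinics would be wider still.

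A shortfall is likely, because the tolerable ICC is so small, but it is not certain. This is a single-group estimate with no test or decision threshold tied to ±3%, so the point is a correction to a stated precision and does not undermine the study.

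**What to change.** Choose one of two routes. Neither needs more women.

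1. **Keep the Harare-wide claim.** State the number of clinics and an ICC range. Restate the precision in Sample size calculations and Table 3 with the design effect. Specify a clinic-adjusted confidence interval for the primary prevalence, suited to a small number of clinics. As an illustration, with 10 clinics and an ICC of 0.005 to 0.02, the 3.0% entry would read about ±3.6% to ±5.0% at 896 women.
2. **Keep ±3%.** State that clinics are treated as fixed strata. Limit the ±3% in Sample size calculations, and the precision claims in the strengths box and the Discussion, to attendees of the participating clinics.

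The first costs one recalculated column and a less favourable stated precision. The second costs a few sentences and a narrower claim.
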